**Estimated study participant accrual period**

Following a review of recruitment data from numerous studies of VMMC (IRDO program data) that we have previously conducted in several sites in the study area some of which have been selected for study implementation in this application, we estimate a conservative average study-wide combined accrual rate of 822 eligible men (25-39 years) per month across the 45 sites (18-19 men per Location per month).

# DATA MANAGEMENT PLAN

IRDO has a well-developed data management office fully equipped with database systems for information management. The office supports all research and program activities for about 30 districts where IRDO is implementing VMMC in Nyanza and other parts of the country. These systems allow all sites to key information into the same main database and permit integration with a variety of different statistical applications such as STATA and SPSS. Data shall be entered directly into pass-word protected computers from paper copies by trained study data staff at the district level and linked to the central IRDO data management office (using the IRDO internal mail server). Paper copies will be secured in the data storage rooms with restricted access. Back up of electronic copies to external source shall be done daily with each update and secured by the data manager.

## Quality assurance of data entry

The data manager will periodically run data cleaning syntaxes to capture errors not detected by the in-built data quality controls. The systems also allow for rapid and accurate data collection and retrieval. Demographic, clinical and laboratory data will be collected by the study nurses or clinical officers using standardized questionnaires and entered directly into a centralized database from the sites. Before data entry, the questionnaires will be cross-checked by data supervisors for accuracy, and obvious errors corrected. Data forms quality will be assured in the following ways;

1. Paper forms will be reviewed for completeness before concluding visits with patients. The staff conducting interviews will check all the responses for missing or incorrect entries. The supervisors will also do random checks on forms for completeness and inconsistencies.
2. Paper forms with errors will be returned to the field staff to verify entries where possible.
3. Paper forms with errors will be presented during a bi-weekly study staff meeting to review errors and provide additional training to mitigate continued mistakes.
4. Data checks will be programmed to prevent entry of data values that are illogical, or when numeric values are entered rather than text and vice versa. The interviewer will be asked to check inconsistent and unlikely, but possible, responses (e.g., Age or marital status).

As part of quality control during data collection, we will engage research assistants to conduct data validation (go back to some sampled households to confirm the accuracy of the data collected previously). If, for example, a household previously documented as having no eligible men is found to have 2 eligible men during validation, the 2 eligible men will be listed and reached with the intervention; this will be done at the validation/listing visit or at a later day/time convenient to the participant. Similarly, if a household is found to have fewer eligible men during a data validation visit, then the enumeration data will be updated to reflect this change.

## Data storage and retention

Both hard and soft copy data will be stored in locked cabinets with limited access by data staff, technical support team, and CDC/KNH IRBs when indicated. To maintain privacy and confidentiality, participants will be identified using the Unique ID number. The code linking the ID number to individual identifying information will be kept in a separate secure location by the project coordinator. The ID number will be the only identifier captured on the data questionnaires and in the computerized database. Following completion of all data collection, the data forms will be archived at IRDO’s head office. One year following completion of the project, identifiers will be removed from the data. Hard copy tools will be retained for five years while electronic copies will be destroyed after ten years.

## Data Ownership and Sharing Policy

IRDO will own the project data, and the study PI, Co-PI and the funding agency (CDC) will have "rights" to access and use the data. The PI, [name], who is also the director of Impact-RDO, will have physical custody of the data on behalf of the organization. All users of IRDO data are required to acknowledge the sources of their data and to abide by the terms and conditions under which they accessed the original data.

## Data Analysis:

***Aim 1:*** ***Compare the rate of uptake of VMMC services by men aged 25-39 years exposed to Inter-Personal Communication, Designated Service Outlets, and IPC+DSO.***

The main outcome measure of this study is VMMC uptake. To assess the rate of uptake of VMMC services by uncircumcised men aged 25-39 years, we will compare the proportion of men who accept to be circumcised across the intervention arms. Specifically, the proportion of men accepting to be circumcised in each of the three arms will be compared to the proportion accepting circumcision in the no intervention group. P-values will be adjusted for multiple comparisons using the Bonferroni method. In order to take into account the clustered nature of the data, we shall also employ statistical methods suitable for analysis of cluster-randomized trials, namely the multi-level logistic regression model via the generalized estimating equations (GEE) approach with a random intercept. The random intercept term will represent the differences in true log-odds between the Locations. Odds ratio of VMMC uptake comparing intervention groups to the control group with the same underlying uptake rate will be estimated. This model will simultaneously assess individual-level and Location-level factors associated with uptake of VMMC as well as the effect of the interventions. Most importantly, it will enable the assessment of the intervention at the level at which randomization occurred: the Location level.

As outlined above under Phase 4, we shall conduct an endline survey in all households with men aged 25-39 years to establish the post-intervention MC uptake, and for those circumcised, collect information on when and where they were circumcised. These will be compared with similar data collected at baseline, using the methods described in the paragraph above. In addition, we shall extract from our database information on age of participants receiving services in each Location/Cluster. We will also have a sense of effectiveness of each recruitment strategy from surrendered referral coupons and from responses to question 1 in Appendix 20 B, asked to men who come for MC and through Appendix 2, the number of men reported and/or verified as circumcised at endline. This information, collected from multiple sources and through multiple approaches, will be compared across different arms of the study.

Program data will be routinely collected on the MoH VMMC client form (Appendix 23) and entered in IRDO data base at the facility level and submitted to the data coordinating office in Kisumu. This is the routine practice. The form has information on clients’ age, sub-location and district which we shall extract for men aged 25-39 years using the Data Extraction Form (Appendix 27). The extracted information will be used to document the ages of clients as well as the districts and sub-locations where they are coming from. We shall use the National 2009 Population Census Report to determine the corresponding Location and village for each sub-location.

***Aim 2: Determine the cost of providing VMMC among the three interventions relative to each other and to no intervention***.

To determine the cost of providing VMMC among the three interventions relative to each other and to no intervention, all expenses (equipment, medical supplies, office supplies, outreach costs, personnel, rent and utilities, local transport, etc.) related to the provision of VMMC will be tracked for every Location and calculated for each man. Cost-effectiveness of providing VMMC under the different interventions will then be assessed by comparing the average/median cost-per-man circumcised across the intervention arms. Detailed analysis plan is included under Costing VMMC in the context of the interventions above.

***Aim 3: Determine, through unlinked de-identified blood samples from bleeding vessels the proportion of men whose HIV status is unknown.***

HIV prevalence among men whose HIV status is unknown will be detected through testing of blood samples from the circumcision wound. HIV prevalence will be calculated by dividing the detected number of HIV by the total number of samples of men whose HIV status is unknown. The association between HIV sero-prevalence will be assessed using prevalence ratio (PR) and prevalence odds ratio (POR); 95% confidence intervals (CIs) will be computed for the ratios. Mantel-Haenszel and random effects model-based estimates of the adjusted prevalence ratios will be computed and logistic regression with random effects will be performed to obtain crude and adjusted prevalence odds of HIV for selected.

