**Sample size Determination**

Sample size for detecting the impact of the interventions on VMMC uptake

Unpublished data from an on-going demand creation study and an HIV community based study show an average of 30% circumcision prevalence in the target group (25-39 years); a corresponding refusal rate of 15% and loss to follow-up of 15%. Using an average MC uptake of 30%, an intra-cluster correlation coefficient (ICC) of 0.005, and a design effect of 2.5 in sample size formula for cluster studies, we estimated that in order to be able demonstrate at least a 33.3 % increase in the rate of VMMC among young adult men in intervention arms when compared to those in control arm with 80% statistical power, and Bonferroni adjusted two-sided $\alpha=(\frac{0.05}{3})=0.017$ following the implementation of study interventions , we will need a sample size of 4,932 men reached with the intervention.

The graph below (*Figure 1)* shows that an effect size equal to 33.3% increase in MC from 30% to 40% will require about 1233 participants per study arm (total 4932), while an effect size equal to 50% increase in VMMC from 30% to 45% will require 573 participants per study arm (total 2292).

Adjusting for refusal rate of 15% and a loss to follow up of 15%, suggests contacting 1603 per study arm resulting in a total of 6412 uncircumcised men aged 25-39 years.

Fig.1 shows a range of sample size requirements for detecting various percentage increases (effect sizes) in VMMC uptake due to the interventions assuming causal effect, and for an 80% power, a 1.7% significance level and a two sided test.

[figure not shown]

Figure 1: Sample Size Vs Percentage Increase in MC Uptake

Selection of Clusters (Locations):

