2. Separating eligible from ineligible Locations: To ensure the populations in participating Locations are as homogenous as possible in terms of ethnicity (which defines circumcising and non-circumcising communities), we spread the map on a flat surface and systematically identified and excluded 37 Locations: 34 bordering traditionally circumcising communities in Kuria, Gucha, Central Kisii, Nandi, Vihiga, Butere-Mumias and Busia districts, and 3 within cosmopolitan Kisumu city where mixed ethnic communities live. In addition, we excluded 5 Locations in the islands due to poor access. Consequently, we remained with 122 eligible Locations to select from (Fig 2: Map 2).
3. Selecting participating Locations: Of the remaining 122 eligible Locations, we randomly selected the starting point and went through the process of systematically selecting each Location and excluding all the contiguous ones until we identified the maximum possible Locations that did not share a boundary. This exercise was done repeatedly by randomly selecting different Locations as the starting point and seeing how many Locations we ended up with. The goal was to select the highest number while ensuring none is proximal to each other. Based on these selection criteria, 45 was the maximum number of Locations that could be included in the study (Fig. 2: Map 3).
4. Random assignment of participating Locations: The names of the 45 Locations were compiled and submitted to the study Biostatisticians (FO & VS) for randomization.The names were entered into Stata V12 statistical package and a randomization schedule produced using the random-number generator. Using simple randomization to allocate clusters, roughly equal number of Locations (11-12 per arm) was allocated to each of the four study arms (Fig 2: Map 4).

A summary of the steps and the number of locations are shown in *Table 1* below while randomization and distribution of allocation to the study arms by districts are shown in Tables 2 and 3.

**Table 1:** Summary of Selected Study Locations

| **Total Locations in *Luo* Nyanza Province** | 233 |
| --- | --- |
| Locations where IRDO is providing VMMC services | 194 |
| Locations excluded because of an ongoing pilot demand creation study | 30 |
| Locations excluded because they border traditionally-circumcising communities | 34 |
| Locations excluded because of having a multi-ethnic population | 3 |
| Locations excluded because of poor accessibility (Islands) | 5 |

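### Holm's step-down method would keep the 5% familywise bound of the specified Bonferroni adjustment and add power whenever more than one intervention works

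*Protocol*

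**What the plan says.** In the protocol's Data Analysis section, under Aim 1, the proportion accepting circumcision "in each of the three arms will be compared to the proportion accepting circumcision in the no intervention group". That is a family of three comparisons sharing one control arm. The adjustment is then fixed: "P-values will be adjusted for multiple comparisons using the Bonferroni method". The protocol mentions no step-down or ordered procedure and gives no reason for the single-step form.

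Sample size Determination uses the matching level. The trial is sized "with 80% statistical power, and Bonferroni adjusted two-sided" alpha of 0.05/3, rounded to 0.017, and the note to Figure 1 repeats "an 80% power, a 1.7% significance level and a two sided test". For 30% against 40% this gives 1233 men per arm (4932 in all), with a design effect of 2.5. Allocation is close to equal: "roughly equal number of Locations (11-12 per arm) was allocated to each of the four study arms".

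**The concern.** Single-step Bonferroni tests each comparison at 0.05/3 = 0.0167 whatever the other two show. Once one null hypothesis has been rejected, at most two can still be true, and a threshold of 0.05/3 for the rest is stricter than the 5% bound requires. Holm uses that slack. The smallest p-value is tested at 0.0167, the next at 0.025 and the largest at 0.05, stopping at the first failure.

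What is at stake is power for the second and third interventions. Aim 1 asks about each strategy, and the costing section says the results should support scaling up whichever demand-creation approaches are effective. The combined arm also contains both single interventions, so more than one true effect is a plausible outcome. That is the situation in which the choice of method matters.

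**Working it through.** **1. Reproduce the plan's own figure.** Inputs from Sample size Determination: 30% v 40%, two-sided alpha 0.017 (z = 2.387), 80% power (z = 0.842), design effect 2.5. With mean proportion p̄ = 0.35:

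m = [2.387·√(2·0.35·0.65) + 0.842·√(0.3·0.7 + 0.4·0.6)]² / 0.10² ≈ 472.8

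Continuity correction: n = (m/4)·[1 + √(1 + 4/(m·0.10))]² ≈ 492.6, taken as 493. Then 493 × 2.5 = 1232.5, or 1233. The same steps for 30% v 45% give 229 × 2.5 = 572.5, or 573. Both stated figures reproduce, so the sizing and the analysis use the same Bonferroni level.

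**2. Holm keeps the bound.** Suppose k of the three null hypotheses are true. For Holm to make its first false rejection, some true null must have p ≤ 0.05/k. By the Bonferroni inequality the chance of that is at most k × 0.05/k = 0.05, whatever the correlation. Holm's first threshold is Bonferroni's and the later ones are larger, so Holm rejects everything Bonferroni rejects. Both methods reject at least one hypothesis in exactly the same trials.

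**3. Size of the gain with each comparison at 80% power.** Three z-statistics with correlation 0.5 (shared control, equal arms). Mean z = 2.394 + 0.842 = 3.236 for a working arm and 0 otherwise. 2,000,000 replicates.

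| Arms that work | Power per working arm, Bonferroni → Holm | All working arms shown | Actual familywise error |
|---|---|---|---|
| 0 | – | – | 4.5% → 4.5% |
| 1 | 80.0% → 80.1% | 80.0% → 80.1% | 3.1% → 4.2% |
| 2 | 80.0% → 82.8% | 68.7% → 74.2% | 1.7% → 3.9% |
| 3 | 80.0% → 86.4% | 61.1% → 76.6% | no true null |

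**4. The same comparison at the protocol's own size.** Effective n per arm = 1233/2.5 = 493, normal approximation, 1,000,000 replicates. The starting power is a little above 80% because 1233 includes a continuity correction that this test does not use.

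| Uptake in the three arms (control 30%) | Power per 40% arm, Bonferroni → Holm | All working arms shown |
|---|---|---|
| 40 / 30 / 30 | 81.7% → 81.9% | 81.7% → 81.9% |
| 40 / 40 / 30 | 81.8% → 84.5% | 71.0% → 76.4% |
| 40 / 40 / 40 | 81.8% → 87.9% | 63.8% → 78.8% |
| 40 / 40 / 45 | 81.7% → 89.3% | 70.9% → 84.1% |

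The chance of at least one rejection is identical under both methods (95.8% with all three arms at 40%).

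**5. The price.** An arm rejected only by Holm has an unadjusted p-value above 0.0167. An interval at level 1 − 0.05/3 = 98.3% for that arm will therefore include no effect. With all three arms working at 80% power, this happens for at least one arm in about 17.5% of trials.

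**The case against.** The strongest reply is that nothing here is wrong. Bonferroni controls the familywise error, the protocol uses it consistently in sizing and analysis, and the stated 80% power per comparison is met without Holm. All of that stands. A reader might infer that the Bonferroni sentence is an error or that it leaves the trial underpowered. The protocol does not support either reading, since its target is per comparison and it sets none for showing all three arms effective.

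It is also fair to say that the largest gains assume all three arms work. Nothing in the protocol promises that. If only one works, the gain is about 0.1 point.

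A third point is that the familywise error is the same only as a bound. With one or two working arms, Holm's actual error is higher, though below 5%.

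Fourth, Bonferroni decisions agree with simple simultaneous intervals and Holm decisions do not. This is a genuine cost, and the plan should state it.

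Finally, the description of Study Arm 3 also intends to compare the combination with each single intervention. The Aim 1 adjustment sentence follows the three control comparisons, and naming Holm for those does not settle how the other contrasts are handled. That limits the scope of the change without weakening the case for it.

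**Conclusion.** The point holds as an inexpensive efficiency improvement to a valid plan. For the three comparisons with control, Holm is never less powerful than Bonferroni under the same 5% familywise bound. On the 80% basis the gain per working arm is about 0.1 point with one working arm, 2.8 points with two and 6.4 points with three. Power to show all three rises by about 15 points. The chance of finding at least one effective arm is unchanged.

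The ordering of the two methods rests on no distributional assumption. The percentages do. They use a normal approximation, equal arms, a shared-control correlation of 0.5 and, for the second table, the stated design effect of 2.5. They ignore the limited degrees of freedom from 11 to 12 Locations per arm, so they should be read as indicative.

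A reader might also infer that fewer men are needed. They are not, because Holm's first step is still tested at 0.05/3.

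**What to change.** In Data Analysis, Aim 1, replace the Bonferroni sentence with one saying that the p-values for IPC, DSO and IPC+DSO, each against control, will be adjusted by Holm's step-down method and compared with a two-sided 0.05. With ordered p-values p₁ ≤ p₂ ≤ p₃, the adjusted values (capped at 1) are 3p₁, then the larger of that and 2p₂, then the larger of that and p₃.

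Add a second sentence saying that decisions rest on the Holm-adjusted p-values. It should add that 98.3% intervals for the odds ratios are for estimation only and may include no effect for an arm rejected at a later step. The Aim 1 text gives no interval level at present, so this also fills that in.

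Leave Sample size Determination as it is; 0.017 remains a conservative design level. Make the change before outcome data by arm are seen. The cost is two sentences and the possible mismatch between decision and interval. No men, data or further assumptions are needed.

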### Demand creation for all other ages

Because the study targets only older men, demand creation for younger men/boys will continue as part of program work. As such, routine recruitment activities will continue for all men in all Locations; these include distributing information, education and communication materials; conducting road shows and magnet theater events to promote VMMC services; carrying out one-on-one or small group face to face interactions with community members, asking those who have been circumcised to refer others; visiting social events to pass information and invite men for service; using radio to present information of VMMC; and so on.

##

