|  | Implement the three interventions, including collecting information on costing and specimens for unlinked HIV testing. ***Approx. 9 Months*** |  |  | |  | | **x** | | **x** | **X** |  |  |
| **Phase 5** | Carry out endlline survey in all households with men 25-39 years uncircumcised at baseline; interview them; verify their MC status and use baseline data from men aged 25-39 years to determine the impact of the interventions. ***Approx. 3 Months*** |  |  | |  | |  | |  | **x** | **x** |  |
| **Cross-cutting** | Data entry, cleaning and analysis, report writing and manuscripts preparation. ***Ongoing up to 18 Months*** |  |  | | **x** | | **x** | | **x** | **x** | **x** | **x** |
|  |  | | | | | | | | | | | |
| **Sub-Study 4** | Develop SOPs; prepare logistics such as printing study materials. ***Approx. 2 Months*** |  | |  | |  | | **x** |  |  |  |  |
|  | Hire and train RAs. ***1 Month*** |  | |  | |  | | **x** |  |  |  |  |
|  | Enroll male participants in the study. ***Up to 6 Months*** |  | |  | |  | |  | **x** | **x** |  |  |
|  | Follow up male participants. ***Up to 8 Months*** |  | |  | |  | |  | **x** | **x** | **x** |  |
|  | Enroll female partners of the men in the study. ***Up to 6 Months*** |  | |  | |  | |  | **x** | **x** | **x** |  |
|  | Data entry and analysis; manuscripts preparation. ***Ongoing up to 12 Months*** |  | |  | |  | |  | **x** | **x** | **x** | **x** |

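### Aim 1 adds an inferential endline-versus-baseline comparison, tied to impact, that cannot be fitted cleanly and does not test IPC or DSO unless it is made between arms

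*Protocol*

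**What the plan says.** The Aim 1 text under Data Analysis sets the main test first. The proportion circumcised in each of the three intervention arms "will be compared to the proportion accepting circumcision in the no intervention group", with Bonferroni-adjusted p-values and a clustered logistic model. The effect measure is also against Control: "Odds ratio of VMMC uptake comparing intervention groups to the control group with the same underlying uptake rate will be estimated".

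The next paragraph turns to the endline survey, which is to record circumcision status and when and where it was done, and adds: "These will be compared with similar data collected at baseline, using the methods described in the paragraph above". After listing other sources (coupons, the counselling question, verified status), it ends: "This information, collected from multiple sources and through multiple approaches, will be compared across different arms of the study".

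Table 8, Phase 5, describes the endline survey in men uncircumcised at baseline and says staff will "verify their MC status and use baseline data from men aged 25-39 years to determine the impact of the interventions".

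On what happens in every arm regardless of allocation, the section on demand creation for other ages says: "As such, routine recruitment activities will continue for all men in all Locations".

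**The concern.** Aim 1 asks whether uptake differs between an intervention arm and Control. A comparison of endline with baseline asks something else: whether circumcision rose over the study. Circumcision cannot be undone, and uptake is expected everywhere. Besides routine recruitment, all participants are to receive a text reminder and Control men receive the standard booklet at enrolment. A rise from baseline is therefore expected with or without an effect of IPC or DSO.

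The sentence calls for the methods of the preceding paragraph, which are inferential (adjusted p-values and a logistic model), and Table 8 links baseline data to impact. Neither place says that the change is to be contrasted between arms. If an analyst ran the comparison within an arm, background uptake, which Control exists to measure, could be credited to the intervention.

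**Working it through.** **1. The plan's own sample size.** Inputs from Sample size Determination: 30% v 40%, two-sided alpha 0.017, power 80%, design effect 2.5. The pooled two-proportion formula gives n = 473 per arm. With continuity correction, n' = (n/4)[1 + √(1 + 4/(n × 0.10))]² = (473/4)[1 + √1.0846]² ≈ 493. Then 493 × 2.5 = 1232.5, i.e. the stated 1233. The same route for 30% v 45% gives 229 × 2.5 = 572.5, i.e. the stated 573. The trial is sized on a two-sample contrast of arm with Control.

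**2. Can the endline-versus-baseline comparison be fitted?**
- *Trial men.* The participant inclusion criteria require men to be uncircumcised, and Table 8 places the endline survey in men uncircumcised at baseline. Their baseline proportion is 0/n, with log-odds ln(0) = −∞. A logistic time coefficient then has no finite maximum-likelihood estimate.
- *All men.* The Phase 3 baseline criteria carry no circumcision-status condition, so a baseline prevalence (about 30% is assumed) exists for all men aged 25-39. The Phase 5 text, however, surveys only enrolled men not recorded as circumcised. The Data Analysis text speaks of all households with men aged 25-39, and Table 8 of men uncircumcised at baseline. On the Phase 5 or Table 8 definition, the two proportions have different denominators.

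**3. What a within-arm version would do with no intervention effect.** This is an assumed analysis, since the protocol does not spell one out. Take 11 Locations and 1233/11 ≈ 112 men each, alpha 0.05/3 = 0.0167. The stated ICC and design effect do not agree: 1 + 111 × 0.005 = 1.555, while 2.5 needs an ICC of about 0.0135. Both were therefore run.

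For a one-sample t-test of Location uptake u against 0%, SE = √[u(1 − u)/112 × DE / 11]. With 10 degrees of freedom the critical value is about 2.87.
- u = 2%, DE 2.5: SE = √(0.0196/112 × 2.5/11) = 0.0063, ratio 0.02/0.0063 ≈ 3.2.
- u = 2%, DE 1.555: SE ≈ 0.0050, ratio ≈ 4.0.
- u = 5%, DE 2.5: SE ≈ 0.0098, ratio ≈ 5.1.
- u = 30%, DE 2.5: SE ≈ 0.0206, ratio ≈ 14.5.

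Simulated rejection rates (beta-binomial Locations, no intervention effect):

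| Background uptake | ICC | Within-arm test v 0% | Arm v Control |
|---|---|---|---|
| 2% | 0.005 | 0.95 | 0.015 |
| 2% | 0.0135 | 0.75 | 0.016 |
| 5% | 0.005 | 1.00 | 0.017 |
| 5% | 0.0135 | 0.999 | 0.014 |
| 10% | either | 1.00 | 0.015 |
| 30% | 0.005 | 1.00 | 0.013 |
| 30% | 0.0135 | 1.00 | 0.019 |

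**4. The all-men version.** Compare prevalence from 30% as two independent samples, with effective n = 1233/2.5 = 493. Rejection is 0.017 with no background rise, then 0.04, 0.24 and 0.82 for rises of 2, 5 and 10 points. If the same men are measured twice but tested as unpaired with design effect 2.5, uptake of 2%, 5% and 10% among the uncircumcised gives 0.00, 0.001 and 0.85. Uptake of 5% among the 70% uncircumcised is a rise of only 0.70 × 5 = 3.5 points, and the unpaired test ignores the positive pairing. This form is much less affected at low uptake.

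**The case against.** A reader might infer that the protocol determines impact by a within-arm before-after test, with a null of no change over time, and that such a test would be run even in Control. The documents do not support that. The main contrast, the odds ratio and the sample size are all arm against Control, and the costing section takes Control as reference for the primary outcome. The Aim 1 text stresses that the model "it will enable the assessment of the intervention at the level at which randomization occurred: the Location level". The sentence on baseline data points back to these methods, and its paragraph closes with a comparison across arms. No passage states a one-arm test or its null.

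Table 8 also has an innocent reading. Its Phase 1 row says the baseline work establishes prevalence and the denominator, so baseline data may serve impact simply by defining who was uncircumcised.

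The rejection rates near 100% belong to assumed Location-level t-tests, not to a named analysis, and one all-men version falls below nominal at 2% and 5% uptake. Which covariates to adjust for is often left to a statistical analysis plan.

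All of this stands against the stronger reading. It does not clear the sentence itself, which plans an inferential comparison without naming the contrast. Comparing change between arms does not rescue it as written either. In men who all start at 0%, change from baseline is just endline uptake, so the between-arm comparison of change in proportions repeats the main analysis, while a logistic time term still cannot be estimated.

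**Conclusion.** The concern holds in limited form. The randomised analysis is sound and keeps its error rate: simulated rejection is 0.013 to 0.019 against a nominal 0.0167, whatever the background uptake. The added endline-versus-baseline comparison is badly fixed. In trial men it cannot be estimated by the named logistic model, and with all men at baseline the denominators differ. If run within an arm, it measures background uptake rather than the effect of IPC or DSO.

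The size depends on that last condition. A Location-level test against 0% would reject in about 75% to 95% of trials at 2% background uptake and nearly always at 5% or more. An all-men prevalence test ranges from below nominal to about 0.24 for rises of up to 5 points. These figures assume no intervention effect, 11 Locations of 112 men, an ICC of 0.005 or 0.0135, and some background uptake. With no background rise, the independent-samples prevalence test stays at nominal.

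**What to change.** In the Aim 1 text under Data Analysis, replace the sentence on comparison with baseline. State that impact is judged only by the randomised contrast of each intervention arm with Control at endline, among men uncircumcised at baseline. Enter each Location's Phase 3 circumcision prevalence as a covariate in that model, which already allows for Location-level factors. Show change from baseline within arms descriptively, without p-values. Reword the Phase 5 row of Table 8, where it says staff will "use baseline data from men aged 25-39 years to determine the impact of the interventions", so that baseline data define the denominator and supply the covariate.

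The cost is two reworded sentences and one covariate from data already planned. No extra men, visits or measurements are needed.
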